### Analyses

Descriptive statistics (means ± SD or median and interquartile range in case of a skewed distribution) will be used to describe the whole study sample with regard to demographics, drug use and reason for previous hospital admission. The analyses will be conducted according to the intention-to-treat principle. To assess the impact of the intervention, multilevel linear and logistic regression analyses will be conducted to study differences in outcome measures between patients of the intervention and control pharmacies. Using multilevel analyses enables taking clustering of observations of participants receiving care from the same GP and for repeated measurements within one subject in account. Differences in changes between groups are measured with 95% confidence intervals. We will adjust data for possible confounders and effect modifiers (age, sex, ethnicity, level of education). Separate analyses of effect modifiers and mediators will be conducted in order to gain a better understanding which subgroups benefit most from the intervention. Confidence intervals of differences in costs between groups will be estimated using bootstrapping methods. (Bootstrapping statistics is a general method for performing statistical analyses without making strong parametric assumptions [32].

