**Methods/Design:**

A randomized controlled trial will be performed. Community pharmacists will be randomized into a control group and an intervention group. 342 Patients, aged over 60 years, discharged from general and academic hospitals, using five or more prescription drugs for their chronic disease will be asked by their pharmacy to participate in the study.

Patients randomized to the control group will receive usual care according to the Dutch Pharmacy Standard. The medication of patients randomised to the intervention group will be reviewed by the community pharmacist with use of the national guidelines for the treatment of diseases, when patients are discharged from the hospital. The Pharmaceutical Care network Europe Registration form will be used to record drug related problems. Trained pharmacy technicians will counsel patients at home at baseline and at 1,3,6,9 and 12 months, using Cognitive Behaviour Treatment according to the Theory of Planned Behaviour. The patient's attitude towards medication and patient's adherence will be subject of the cognitive behaviour treatment. The counselling methods that will be used are *motivational interviewing *and *problem solving treatment*. Patients adherence towards drug use will be determined with use of the Medication Adherence Report Scale Questionnaire. There will be a follow-up of 12 months.

The two primary outcome measures are the difference in occurrence of DRPs between intervention and control group and adherence with drug use. Secondary endpoints are attitude towards drug use, incidence of Re-hospitalisations related to medicines, functional status of the patient, quality of life and the cost-effectiveness of this intervention.

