## Background

Drug related problems (DRPs) are events or circumstances involving drug therapy that actually or potentially interfere with desired health outcomes [1]. Examples of DRPs are contra-indications, interactions, adverse drug reactions (ADR) and inefficacy of treatment. Causes for these problems can be prescription errors, non-compliance with treatment and the specific effects of drugs in patients. Factors that increase the risk of DRPs are polypharmacy, co-morbidity, aging, non-adherence and lack of coordination between different treating physicians.

An increased number of prescribed drugs (polypharmacy) strongly increase the risk of DRP. Runciman found a correlation between increases in medication use and rates of adverse drug reactions associated with hospitalization [2]. Another recent review of studies of the effect of polypharmacy on the health state of elderly people has shown that multiple drug use is a strong predictor of hospitalisations, nursing home placement, death, hypoglycaemia, fractures, impaired mobility, pneumonia and malnutrition [3]. Furthermore, Leendert et al suggest that elderly people have a higher risk of hospitalisation caused by DRP, especially if they use have 4 or more co-morbidity [4].

Elderly people >75 year seem at higher risk for hospitalisation caused by DRP [2]. A study conducted in the Netherlands examined the occurrence of hospitalisations that were related to medication. This study showed 12.793 acute hospital admissions per year of which 714 admissions were medication related and 332 of these admissions were preventable. They calculated that 19.000 hospital admissions per year were related to medication and were preventable [4]. Specific risk factors were the number of prescribing physicians [5] and the number of diagnoses [6], the number and combination of several (inappropriate) drugs [6,7] and the use of inappropriate drugs [8-11].

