### Outcome Measures

#### Primary outcome measures

Using a checklist including common drug problems, the prevalence of DRP in patients of control and intervention pharmacists will be determined at base-line and at 12 months by a team of independent clinical pharmacologists. The identification of drug problems by community pharmacist will be assessed on the basis of a structured interview of the patient and the medication overview of the patient registered in the pharmacy information and administration system.

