#### Secondary outcome measures

##### Incidence of Re-hospitalization

The total incidence of hospital re-admissions possibly related to medicine during the study period is measured. The incidence of hospital admissions will be derived from general practitioners medical record and determined by self report. The relation to drugs will be derived using a list of selection criteria. Hospital admissions will be classified as related to drugs if:

▪ It is explicitly clarified in the medical notes that the admission is drug related. The specialist of the patient will be consulted to clarify the relation to drugs.

▪ The patients' physician, when asked, indicates that the admission was drug related.

▪ To classify the causality of the hospital admission to the drug, the Naranjo algorithm will be used. The Naranjo algorithm or Naranjo Scale is a questionnaire designed by Naranjo *et al *for determining the likelihood of whether an ADR is actually due to the drug rather than the result of other factors [25]. The causality will be determined by the project leader.

All participating patients are asked to complete 3 validated questionnaires during the research year. The first questionnaire will be sent to the patients one week before the first counselling visit of the pharmacist. The second questionnaire will be sent at 6 months, the third questionnaire will be sent at 12 months. It will take approximately 30 minutes to complete one questionnaire.

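### The plan compares changes between groups without using the baseline outcome as a covariate, and leaves number of drugs and PTAM out of the model

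*Protocol article*

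**What the plan says.** The Analyses section of the protocol article fixes three things that matter here.

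- Model: "multilevel linear and logistic regression analyses will be conducted to study differences in outcome measures between patients of the intervention and control pharmacies". The multilevel structure is also meant to take account of clustering by GP and "for repeated measurements within one subject in account".
- Contrast: "Differences in changes between groups are measured with 95% confidence intervals".
- Adjustment: "We will adjust data for possible confounders and effect modifiers (age, sex, ethnicity, level of education". Drug use appears in this section only among the descriptive statistics.

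Baseline data are planned. Under Primary outcome measures, "the prevalence of DRP in patients of control and intervention pharmacists will be determined at base-line and at 12 months". For the questionnaires, "The first questionnaire will be sent to the patients one week before the first counselling visit of the pharmacist", with further ones at 6 and 12 months. The paragraph on MARS gives no time points, so a baseline MARS score is inferred from that schedule.

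The Background states: "An increased number of prescribed drugs (polypharmacy) strongly increase the risk of DRP". Study Population sets a minimum of five chronic drugs and no maximum. Treatment allocation says that pharmacists are randomised within PTAMs, of which there are ten. According to the abstract, patients "will be asked by their pharmacy to participate in the study".

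**The concern.** When an outcome is measured before and after, subtracting the baseline value forces its coefficient to be 1. Using it as a covariate lets the data set the coefficient. The second is more precise at any correlation below 1, and it treats an imbalance that fades over time correctly.

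Regression to the mean is credible in this trial. Patients enter just after discharge, when, as the Background describes, drugs have been stopped, added or re-dosed. DRPs could be unusually frequent at that moment and decline in both arms. If the intervention arm started higher, by chance or because of whom its pharmacies invited, a change score would credit part of that decline to the intervention.

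The adjustment list also omits a predictor that the article itself calls strong, and the stratum within which randomisation took place. Precision is scarce (first step of the working), so an avoidable loss matters.

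**Working it through.** **Context: the planned size.** The concern disputes no stated figure, but the sample size shows how much precision there is to lose. The inputs under Sample size are 30% against 20% (one third lower), alpha 0.05 (two-sided assumed), 80% power and a 15% loss for clustering.

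- Unpooled formula: (0.30×0.70 + 0.20×0.80) × (1.960 + 0.842)² / 0.10² = 290.4 per arm. Then 290.4 / 0.85 = 341.7.
- So 342 matches a per-arm number, while the article gives it as the total. That is a separate matter.
- With 171 per arm, power is about 57% before the clustering allowance and about 50% after it (171 × 0.85 = 145 per arm).

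**Precision, continuous outcome.** Let r be the baseline to follow-up correlation. The documents do not give it, so 0.3 to 0.7 is assumed. Variances are taken as equal at both times and clustering is ignored. In units of the outcome variance:

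- simple change score: 2(1 − r)
- baseline as covariate: 1 − r²
- ratio, adjusted to change: (1 + r)/2

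| r | change | adjusted | ratio | 342 × ratio |
|---|---|---|---|---|
| 0.3 | 1.40 | 0.91 | 0.65 | 222.3 |
| 0.5 | 1.00 | 0.75 | 0.75 | 256.5 |
| 0.7 | 0.60 | 0.51 | 0.85 | 290.7 |

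The last column is the number of baseline-adjusted patients that 342 change scores are worth. Below r = 0.5 the change score has more variance than the 12-month value alone, which has variance 1.

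**Bias from a baseline difference D, with no treatment effect.** If the difference regresses, the expected follow-up difference is rD. The change score then gives rD − D = −(1 − r)D, and baseline adjustment gives rD − rD = 0. If the difference is stable, the follow-up difference stays D. The change score then gives 0, and adjustment for the baseline value alone gives D − rD = (1 − r)D. With D = 0.2 SD:

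| r | regressing: change | regressing: adjusted | stable: change | stable: adjusted |
|---|---|---|---|---|
| 0.3 | −0.14 | 0 | 0 | +0.14 |
| 0.5 | −0.10 | 0 | 0 | +0.10 |
| 0.7 | −0.06 | 0 | 0 | +0.06 |

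Neither method is safe in every case. A stable imbalance is best handled by including its cause, here the number of drugs, as a covariate.

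**Binary DRP.** This was simulated with 342 patients in total, no clustering, 600 runs per scenario and an assumed log odds ratio per drug of 0.1 to 0.2.

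| Analysis | SE of risk difference | Power |
|---|---|---|
| change | about 0.063 | 36–42% |
| 12-month only, unadjusted | about 0.046 | 59–64% |
| baseline + number of drugs | about 0.046 | 61–65% |

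With one extra drug per intervention patient and no true effect, the unadjusted comparison was biased by +0.018 to +0.035. The change score and the adjusted analysis both had bias of about 0.

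The simulated correlation between baseline and 12-month DRP status was low. Setting (0.0628/0.048)² = 1.71 equal to 2(1 − r) gives r of about 0.14, and (0.063/0.0466)² = 1.83 gives about 0.09. If DRP status tracked more strongly, the change score would lose less and the baseline covariate would add more.

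**The case against.** The best defence is that the article does not commit to a simple change score. It names a multilevel model with repeated measurements. A model of that kind with a common baseline mean in both arms also yields a difference in change, with nearly the efficiency of baseline adjustment. This stands in part: the loss in the working applies only if change is computed by subtraction, or with baseline means left free by arm. The article does not say which is meant, and its printed covariate list omits the baseline value.

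Four stronger readings are tempting, and the documents do not support them.

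- A reader might infer that the baseline outcome is ignored. It is not: a change score uses it with coefficient 1.
- A reader might infer that any imbalance from recruitment goes uncorrected. A stable one is removed, and the simulation shows this for drug count.
- A reader might apply the gain of 1 − r² over an unadjusted comparison to DRP. That formula is for continuous outcomes. In the simulation the gain was about 2 points of power, and a logistic model does not follow it.
- A reader might take it as documented that pharmacies knew their allocation when inviting patients. The article gives no such order. It is a fair inference from pharmacy-level allocation and invitation by the pharmacy, and no imbalance is reported.

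Baseline DRP could also be ascertained differently by arm if identification by trained intervention pharmacists feeds into it. That caution is fair but does not favour the change score, which carries any such difference with full weight.

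Finally, Study Population says that pharmacists check for five or more drugs, not that they record a count. The count should still be recoverable, because the pharmacy system holds each patient's medication overview.

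**Conclusion.** The point holds as a correctable weakness in a stated method. The contrast is a difference in changes, the baseline outcome is not a covariate, and number of drugs and PTAM are absent from the model.

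For MARS and other continuous scales, a simple change score wastes 35%, 25% or 15% of its variance at r = 0.3, 0.5 or 0.7. For a regressing imbalance of 0.2 SD it leaves a bias of 0.14, 0.10 or 0.06 SD. For binary DRP the change comparison is also less precise, but the remedy then gains little over a plain 12-month comparison when tracking is weak.

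These sizes rest on assumed correlations, on equal variances, on ignoring clustering, and on change being taken by subtraction. Selective recruitment is a plausible source of imbalance, not an established one, and no covariate set would remove it fully.

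**What to change.** For every outcome with a baseline, make the primary estimate the follow-up outcome by arm, within the multilevel model, with these covariates:

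- the baseline value of the same outcome (DRP status or count, MARS score);
- number of chronic drugs at inclusion, counted before the medication review can alter it;
- PTAM;
- the demographics already listed.

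A repeated-measures model with a common baseline mean in both arms is an equivalent choice, provided the plan says so. The difference in changes can stay as a sensitivity analysis, because it does better when an imbalance is stable.

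The costs are small. The logistic model will give a conditional odds ratio, which the plan should state. The model also grows. PTAM as fixed effects takes 9 terms; with arm, baseline, drug count and at least four demographic terms, that makes at least 16. The planned rates give 171 × 0.30 + 171 × 0.20 = 85.5 patients with a DRP, or about 5 per parameter. PTAM as a random effect leaves 7 terms and one variance, so 85.5 / 8 = about 11. No new data collection should be needed, provided that baseline MARS is in the first questionnaire and the drug count can be taken from pharmacy records.

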## Discussion

This article presents a description of a RCT, which aims to investigate whether a multifaceted intervention by the community pharmacist existing of medication review and CBT to increase drug adherence after discharge from the hospital, is effective in reducing DRPs among elderly patients of 60 years and older using five or more prescript drugs for a chronic disease. The present paper will provide other researchers working on this subject, GPs, pharmacists, medical specialists, other health care providers and policy makers an overview of the RCT. This enables them to critically review the methodological quality, the background theory and the practical issues of the RCT. Previous studies have shown that pharmacist initiated interventions are effective in reducing DRPs [33,34]. To our knowledge this is the first study that will combine two strategies: medication review and CBT to reduce the occurrence of DRPs among patients who are at higher risk to these problems. Studies have shown that medication review is an effective method in decreasing the occurrence of DRPs [34]. Most studies have studied the effect of medication review on patients in all age categories on the occurrence of drug problems. In this study we will determine the effect of medication review on the occurrence of DRPs among elderly patients who are discharged from the hospital. This has not yet been studied before. Furthermore, we expect that patient CBT based on motivational interviewing and problem solving treatment will increase or sustain patient's drug adherence after hospital discharge and therefore lowers the risk of having a DRPs and re-hospitalisation.

There are several practical limitations associated with performing medication review. Detecting and solving drug related problems by health care workers such as community pharmacists is a time consuming process [35]. In order to make any changes in the drug regimen, the pharmacist has to contact the general practitioner first, which is time consuming. Furthermore, community pharmacists have to communicate the changes that are made with their patients. Because of their busy daily schedules, it may be possible that pharmacists do not find that medication review has a priority. Another major limitation is the possible bias in the detection and solving of DRPs by the different community pharmacists since all pharmacists have different experiences in performing a medication review. Some pharmacists will therefore identify more or less drug related problems than others, depending on the limited time. In addition, another limitation of the intervention is that the performance of CBT might differ between pharmacy technicians because of the interview skills they have. It is therefore difficult to decide whether all patients receive the same therapy sessions. We will try to reduce the differences between the pharmacy technicians, by using a structured interview protocol and motivational interviewing and problem solving treatment courses. A major strength is by combining medication review and CBT sessions can lead to a possible improvement of detection of drug related problems. The CBT sessions with patients discharged from the hospital will be helpful in detecting drug problems such as side effects and non-compliance, and thus lead to a better communication between the community pharmacy and patient.

A limitation of the study design is that there is no literature available that describes an evidence based method that can be used by pharmacists to report the quality of the pharmacotherapy or how to detect and solve drug related problems. However, we will apply in this study a method of prescription problems which we can test on feasibility and effectiveness. Strength of this study design is that it is a RCT.

The inclusion of the patients has been performed between in January 2008 and March 2009. Duration of the study will be one year. If this study has a positive effect in reducing the occurrence of drug related problems, it can be implemented as within a community pharmacy. This service can be specially implemented for patients discharged from the hospital, in order to minimize the occurrence of DRPs.
